## **Trial design**

A placebo controlled double-blind crossover group randomised controlled trial will be conducted. The placebo will be a non-active substance.

## **Study sites**

Participants will be recruited from the Nthabiseng HIV Clinic at the CHBH, who have more than 5000 patients on their books, the HJH HIV clinic (more than 7000 patients on ARV therapy), and the palliative care clinic and outreach services. The clinics are Government ARV accredited sites, and see patients who are not yet eligible for ARV therapy. The palliative care clinic and outreach services see patients who are on ARV therapy and those who have declined, no longer on the ARV. The potential participants will be recruited by a non-clinic staff member. Initially recruitment will occur at the CHB hospital. If required then recruitment will take place at the HJH. All the clinics and services are at the hospital site or hospital outreach. The interviews, examinations and data processing will take place at the CHB palliative care centre for excellence.

## **METHODS**

### **Sample size calculations**

These have been calculated by a statistician, in the Wits School of Public Health.

The sample size will be determined with the following variables considered:

90% power,  $\alpha=0.05$ , effect is difference of 2 on a 0-10 scale; variance is 2SD. Variability of the distribution of the population was estimated from existing local clinical data and from previous estimates in the literature. The size of the placebo effect was estimated after considering the literature. For a cross-over design 46 participants will be required. Assuming two distinct sub-populations, those stable on ARV therapy and those not on ARV therapy and a loss to follow-up of ~10%.

**Enrolment target is 124 participants:** 62 on ARV therapy and 62 not on ARV therapy

### **Randomisation**

The randomisation allocation provided by the manufacturers of the placebo and active product. Participants will receive either regime A or regime B in a random manner. One regime will contain 6 weeks of active substance, followed by three weeks washout, then with 6 weeks of placebo, the other will contain 6 weeks of placebo followed by three weeks washout, then 6 weeks of active substance. Patients will be randomly allocated via a concealed allocation; the randomisation will be generated by block randomisation methods.

[figure not shown]

### **Inclusion and exclusion criteria:**

The following criterion will be used to select patients:

1. Confirmed and documented HIV positive status, either on Arv therapy or not on ARV therapy
2. Diagnosed with moderate to severe peripheral neuropathy using the BPNS and DN4 screening tools and scoring  $\geq 4$  on an 11 point Likert scale visual analogue scale.
3. Age above 18 on the date of recruitment
4. Ability to mentally and physically understand to make informed choice to participate in the study

All patients who fit the above criterion will be eligible for participation.

### **Exclusion Criteria**

All conditions which are likely to cause confounding will be excluded from the study, together with conditions which are likely to cause drug interactions.

- Severe pain from DSN caused by ARV drugs which warrants a change in regime
- Already taking amitriptyline drug, or has taken the drugs at least three weeks prior
- Limb amputation
- Kaposi sarcoma of the lower limbs
- Current post- herpetic neuralgia or herpes zoster
- Pregnancy or intention to fall pregnant
- TB treatment
- Malignancy not related to HIV
- Major psychiatric disorders including mania or epilepsy
- Clinically significant renal failure
- Diabetic neuropathy
- Clinically significant liver failure or past history as defined by encephalopathy, oedema and jaundice

- Patient in extreme pain or exhausted
- Participating on another trial or study
- MAOI, other tricyclic antidepressants or anti-epileptic drugs
- Recent myocardial infarction, arrhythmias, heart block
- History of urinary retention, urinary hesitancy or closed angle glaucoma

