## Trial abstract

A double blind randomised controlled trial to assess the effectiveness of amitriptyline compared to placebo in the management of moderate to severe HIV- related peripheral neuropathy. A cross over design will be used and 124 adult male and female volunteer participants with moderate to severe HIV related neuropathic pain will be followed up for a total of 15 weeks. Sixty two participants will be clinically and virologically stable on ARV drugs and 62 will not be in ARV therapy or intending to start in the next four months. In the first six weeks participants will be given either amitriptyline or identical looking placebo titrated to either effect or a maximum dose of 150mg. Then following a three week 'washout' period, participants will be 'crossed-over' to the other arm and titrated to either effect or a maximum dose for 6 weeks. Pain intensity will be measured on a daily basis and recorded into a pain diary by the participant and regular telephonic contact will be maintained between the study nurse and the participants. Pain intensity using tools validated for neuropathic pain, as well as other data will be collected at face to face interviews at each of the 5 scheduled follow up visit. Data collected will include information on adverse events, physical functioning and quality of life.

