### ***Clinical issues of importance when considering drug of choice***

Any drug candidate for treatment of DSN should not have interaction with ARV therapy, either documented or theoretical. For example carbamazepine is not recommended for use with ARV therapy because of drug interaction with nucleosides(13). The SA DOH first and second line recommendations or commonly used drugs by people with HIV such as contraceptive pills, fluconazole do not have listed drug interactions with amitriptyline. Other trials have not found that amitriptyline adversely affects viral load or CD4 counts, or any other blood marker for safety. Therefore it is not considered necessary in this trial to measure viral load. The side effects of the drug should be considered. The Schlay trial and the Kiebertz trials noted that amitriptyline was well tolerated at dosages of up to 100mg per day(6;7). This concurs with local experiences. The pill burden, drug formulation and side effects should also be considered and are proposed to be acceptable for amitriptyline. Since people with HIV often experience multiple pains occurring concurrently, a screening tool validated for HIV related DSN will be used and pain treatments will be documented. Primary

outcome measures will not be changes in mood, sleep or quality of life, since these may be attributable to treatments of other pains.

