## **Product information**

Amitriptyline has antidepressant properties belonging to the tricyclic group. Indicated use is for management of depressive illness, nocturnal enuresis, and pain relief in chronic pain syndromes. It is well absorbed orally, has a half life of between 10 and 50 hours (average 16 hours). It is extensively metabolized in the liver, involving microsomal hepatic enzymes and eliminated over several days, primarily in the urine.

Contraindications are early post-myocardial infarct period and heart block. Use with caution is recommended in patients with: hyperthyroidism, or on thyroxine therapy; arrhythmias; epilepsy; prostatic enlargement; closed angle glaucoma or impaired liver function.

Amitriptyline has no drug interactions with ARV therapy. Drug interactions include those with antihistamines, antipsychotics, anti-cholinergic type anti parkinsonian agents, cimetidine, fluoxetine, paroxetine, steroids, including oral contraceptives and MAOI drugs. It is not to be used in pregnancy.

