### ***Cross over design***

A cross over design is proposed for the following reasons: HIV has a complex disease course, and it is acknowledged that there may be many different mechanisms for the DSN so it is desirable if the participant acts as their own control. It is considered that the disease course will not significantly deteriorate in the follow up period of 15 weeks, although the baseline pain intensity will be measured at the start of each treatment intervention. It is anticipated that the follow up period is not too long to see a significant attrition rate. There will be two sub-groups: those stable on ARV with DSN and those not on ARV drugs. Secondly, the disease process is fairly stable over the proposed 14 weeks and the survival times for most participants will be more than proposed trial period.

Washout period: The SAMF 8 cites a plasma  $t_{1/2}$  of 10-50 hours, but also notes that the nortriptyline metabolite is active. The rule of thumb would be 5 half-lives, but in this case, you'd need to track down the metabolite's elimination. (Handbook of Basic Pharmacokinetics including Clinical Applications (6th edition). Ritschel WA and Kearns GL. APHA, Washington, 2004) gives a  $t_{1/2}$  for nortriptyline of 14-90 hours. On that basis, you'd be looking at a wash-out of at least 450 hours, or 18.75 days. Personal correspondence [name]

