## **Population**

### ***ARV and no ARV***

The possibility of effect for subpopulations will be factored into the trial design, with a sample size calculated to stratify into two groups, those stable on ARV and those not on ARV drugs. Changes in ARV regime may interfere with DSN, so become confounding factors and difficult to interpret. Thus only those stable on ARV drugs for three or more months will be considered eligible.

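### The prior-amitriptyline exclusion is reversed as written, and the eligibility lists omit the antiretroviral (ARV) conditions set elsewhere in the protocol

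*Protocol*

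**What the plan says.** **Prior amitriptyline.** The Exclusion Criteria list bars a patient "Already taking amitriptyline drug, or has taken the drugs at least three weeks prior". The same item stands in the copy of the list under Gender considerations, so neither copy corrects the other. Under Cross over design, the protocol works out the clearance time for the active metabolite: "you'd be looking at a wash-out of at least 450 hours, or 18.75 days". Randomisation and Ethics review then set three weeks between the two treatment periods.

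**ARV status.** The first inclusion criterion asks for "Confirmed and documented HIV positive status, either on Arv therapy or not on ARV therapy", with no condition on duration, stability or plans. The inclusion list ends: "All patients who fit the above criterion will be eligible for participation". Two other places are stricter. ARV and no ARV says that "only those stable on ARV drugs for three or more months will be considered eligible", and gives as its reason that regimen changes confound the neuropathy and are hard to interpret. The Trial abstract says of the other stratum that "62 will not be in ARV therapy or intending to start in the next four months".

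**Contraceptive pills.** Product information includes among the interacting drugs "cimetidine, fluoxetine, paroxetine, steroids, including oral contraceptives and MAOI drugs". The section on clinical issues in choosing the drug says that "contraceptive pills, fluconazole do not have listed drug interactions with amitriptyline".

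**The concern.** A washout rule exists to keep out recent exposure. Here the words *at least* put the boundary on the wrong side: distant use excludes and recent use does not. A patient still clearing the drug could give the first baseline pain score, while a patient long since clear of it would be turned away. The protocol describes amitriptyline as widely used for this condition in South Africa, and the palliative care services that supply participants offer it. Past users among candidates are therefore foreseeable, though the document gives no figure for how many.

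The ARV gap affects the crossover comparison and the stratification. Each participant is their own control, which assumes that the background stays fixed over both periods. Someone who starts or changes ARV between the first and second period has a different background in each. Someone counted in the no-ARV stratum who starts treatment mid-trial no longer belongs to the stratum in which they were counted (62 per stratum). The protocol states the conditions that guard against this, but not in the lists that a screener would apply.

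**Working it through.** **1. The protocol's own washout figure.** Inputs from Cross over design: five half-lives as the rule of thumb, and a nortriptyline half-life of 14 to 90 h.

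5 × 90 h = 450 h; 450 / 24 = 18.75 days. This matches the stated figure exactly, so the protocol designs to the top of the range. Three weeks is 21 × 24 = 504 h, and 504 / 90 = 5.6 half-lives.

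**2. Whom the exclusion catches, judged by date of last use.**

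| Last use before enrolment | Literal wording | Washout reasoning |
|---|---|---|
| Still taking | Excluded | Should be kept out |
| Stopped less than three weeks ago | Not excluded | Should be kept out |
| Stopped three or more weeks ago | Excluded | Washed out |

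The second and third rows are the wrong way round.

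**3. What remains after stopping.** Residual fraction = 0.5^(hours since last use / half-life). This assumes simple first-order decline from the level at the last dose.

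| Days off drug | Nortriptyline, 14 h | Amitriptyline, 50 h (its upper value) | Nortriptyline, 90 h |
|---|---|---|---|
| 3 | 2.8% | 37% | 57% |
| 7 | 0.02% | 10% | 27% |
| 14 | about 0 | 1% | 8% |
| 21 | about 0 | 0.1% | 2% |

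For example, 7 days is 168 h. At 90 h, 168 / 90 = 1.87 half-lives and 0.5^1.87 = 0.27. At 14 h, 168 / 14 = 12 half-lives and 0.5^12 = 0.0002.

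**4. ARV conditions against the lists.**

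| Condition | Where stated | In the inclusion list? | In the exclusion list? |
|---|---|---|---|
| Stable on ARV for three or more months | ARV and no ARV | No | No |
| Not on ARV, no intention to start within four months | Trial abstract | No | No |

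The only ARV item in the exclusion list concerns severe ARV-caused pain that calls for a regimen change. It does not cover a recent start, a recent switch or a planned start.

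Follow-up is 15 × 7 = 105 days. Four months is about 4 × 30.44 = 122 days. The four-month condition therefore spans the whole trial, and it is the one that keeps the no-ARV stratum off ARV through both periods.

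**The case against.** The strongest reply is that the intent is plain. The exclusion list opens by saying that likely confounding conditions are excluded, the three-week washout is stated more than once, and the amitriptyline item is probably a drafting slip. The ARV rule is misplaced rather than absent, since the section that states it is itself about eligibility. The closing sentence of the inclusion list precedes the exclusion list and cannot be meant to override everything else. The screening form is not shown and may be worded correctly. All of this is fair, and it limits the claim to what the lists would *permit*. It does not remove the defect: both copies carry the same wording, and a general statement of intent is not a criterion that a screener can apply.

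The exclusion can also be read as any use three or more weeks ago, rather than last use. A long-term user who stopped last week would then be excluded too, and only someone whose whole course fell within the last three weeks would slip through. Every washed-out past user would still be turned away, so the wording fails on that reading as well.

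A reader might infer more than the document supports:

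- **That the treatment comparison is biased.** Sequence is randomised. Residual drug at the first baseline, or ARV changes unrelated to allocation, balance across sequences in expectation and act mainly as noise or period effects.
- **That a recent stopper carries 27% of the metabolite.** That holds at 7 days and at the top of the half-life range only.
- **That the protocol says outright that recent amitriptyline users must be kept out.** It does not; this follows from the washout reasoning.
- **That requiring virological stability contradicts not measuring viral load.** Measurement is dropped because amitriptyline was not found to affect viral load, which is a safety argument. Clinic records could show stability; at most, the source of that information is unstated.
- **That every interacting drug named under Product information should appear among the exclusions.** The exclusion list speaks of conditions likely to cause interactions, and a listed interaction need not be an exclusion.

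**Conclusion.** The point holds as a wording defect that gives the wrong result if the lists are followed. The prior-use item works against the protocol's own washout, and the ARV conditions that the protocol sets are missing from the lists.

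The size of the first part depends on the half-life: about 0.02% to 27% residual nortriptyline at 7 days off drug, against about 2% or less at 21 days. This rests on first-order decline and the half-life ranges quoted in the protocol. The number of candidates affected cannot be derived from the document.

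The likely consequences are extra noise, ARV strata that no longer mean what they say, and unnecessary loss of washed-out candidates. Neither a biased treatment estimate nor a loss of power has been shown.

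The disagreement on contraceptive pills is a separate, minor inconsistency. The document does not settle which statement is right, and this review takes no position on it.

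**What to change.** - In both copies of the list (Gender considerations and Exclusion Criteria), reword the item so that it covers current amitriptyline use or use within the three weeks before enrolment, in line with the protocol's own washout.
- Carry the two ARV conditions into the inclusion list as they already stand: three or more months' stability from ARV and no ARV, and no ARV with no intention to start within four months from the Trial abstract. Keep the existing word *stable*; a requirement for an unchanged regimen would be a new rule, not one the protocol contains.
- Align the screening form with the corrected lists.
- Separately, reconcile the two statements on contraceptive pills with each other and with the exclusion list.

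The cost is a few lines of text and a check of one form. A few recent amitriptyline users and recent ARV starters become ineligible, offset by washed-out past users becoming eligible. The change belongs before screening, because a participant randomised under the wrong wording cannot be un-enrolled afterwards.

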## **Study procedures**

### ***Recruitment method***

Patients will be recruited from Chris Hani Baragwanath Hospital HIV clinic, Helen Joseph HIV Clinic and the Palliative care community outreach unit and out-patients clinic. The patients will be actively recruited by the study doctor and nurse, and screened for eligibility. In addition clinic staff will be informed of the study and be able to invite patients who show interest to find out more from the study team. Posters will be displayed in the clinics providing information on the study.

### ***Screening procedure***

Patients agreeing to participate will undergo screening. The following will happen during this visit:

1. Information session on the study. Posters and group recruitments will be supported by one-to one information sessions
2. Assess eligibility for study
3. Written consent will be obtained to have a short eligibility questionnaire administered and a test for ankle reflexes and vibration sense. See appendices
4. Inform participant of eligibility status then either thank participant for involvement in screening and referral to palliative care or other services if appropriate. Or if eligible invite them to information session in the study now or at a time convenient to them.

### ***Baseline procedure***

The following is the procedure for the baseline visit:

1. Detailed information session on the study
2. Time to consider participation and invite questions and clarification
3. If agrees to join study then administer written informed consent. If not or changes mind then thank the participant for their time
4. For those enrolled collection of demographic data(Appendix 3)
5. Collection of clinical data(Appendix 4)
6. Assessment of peripheral neuropathy(Appendix 5);
7. Review eligibility criteria and if still eligible and consenting then randomization will occur
8. Participant will be given arm treatment, pain diary and written and verbal instructions. They will receive an airtime voucher or telephone card for R28 per month for the duration of the study and a telephone number to call should they need to call the study team

### ***Follow up procedures: Day 4-day 15***

At home: one tablet will be taken at night for three nights. On the third day the study nurse will call to enquire as to adverse effects, pain score and any other problems, and advice on the next dosage. If the pain has abated significantly the dose will be left at one tablet at

night. If not, the dose will be increased to two tablets at night for three nights. The same procedure will occur until a maximum of 6 tablets at night has been reached. The participant will continue to take this dose for 4 weeks. A weekly telephone call will be conducted by the study nurse.

|                         |                                                                                                                                                                                                                                                                                                   |
|-------------------------|---------------------------------------------------------------------------------------------------------------------------------------------------------------------------------------------------------------------------------------------------------------------------------------------------|
| Day 3                   | The study nurse will call to enquire as to adverse effects, pain score and any other problems, and advice on the next dosage. If the pain has abated significantly the dose will be left at one tablet at night. If not, the dose will be increased by two tablets at night for three nights.     |
| Day 7                   | The study nurse will call to enquire as to adverse effects, pain score and any other problems, and advice on the next dosage. If the pain has abated significantly the dose will be left at two tablets at night. If not, the dose will be increased to three tablets at night for three nights.  |
| Day 11                  | The study nurse will call to enquire as to adverse effects, pain score and any other problems, and advice on the next dosage. If the pain has abated significantly the dose will be left at three tablets at night. If not, the dose will be increased to four tablets at night for three nights. |
| Day 13                  | The study nurse will call to enquire as to adverse effects, pain score and any other problems, and advice on the next dosage. If pain has abated significantly the dose will be left at four tablets at night. If not the dose will be increased to six tablets at night. I                       |
| Week 3 day 15           | The study nurse will call to enquire as to adverse effects, pain score and any other problems, and advise to stay at the same dosage for the next 4 weeks                                                                                                                                         |
| Visit 3.0 Week 3 day 21 | Visit to study site. Check diary, questionnaire administered, medication check, discussion and information as required with participant, reimbursement, referral as required                                                                                                                      |
| Week 4 day 28           | The study nurse will call to enquire as to adverse effects, pain score and any other problems, and advise to stay at the same dosage for the next 3 weeks                                                                                                                                         |

|                         |                                                                                                                                                                                                                                                                                                                                                                                                                                                                                                             |
|-------------------------|-------------------------------------------------------------------------------------------------------------------------------------------------------------------------------------------------------------------------------------------------------------------------------------------------------------------------------------------------------------------------------------------------------------------------------------------------------------------------------------------------------------|
| Week 5 day 35           | The study nurse will call to enquire as to adverse effects, pain score and any other problems, and advise to stay at the same dosage for the next 2 weeks                                                                                                                                                                                                                                                                                                                                                   |
| Visit 6.0 Week 6 day 42 | 
 
1. Visit to study site Check diary, questionnaire administered, medication check, discussion and information as required with participant, reimbursement, referral as required Collection of demographic data(Appendix I)
 
2. Collection of clinical data(Appendix II)
 
3. Assessment of peripheral neuropathy and other symptoms(Appendix III); if present refer to Palliative care
 
4. Assessment of coexisting pain medication
 
 |
| Week 7 day 49           | The study nurse will call to enquire as to adverse effects, pain score and any other problems                                                                                                                                                                                                                                                                                                                                                                                                               |
| Week 8 day 56           | The study nurse will call to enquire as to adverse effects, pain score and any other problems                                                                                                                                                                                                                                                                                                                                                                                                               |
| Visit 9.0 Week 9 day 63 | Visit to study site Check diary, questionnaire administered, medication check, discussion and information as required with participant, reimbursement, referral as required. Patient to receive new drug pack                                                                                                                                                                                                                                                                                               |
| Week 10 Day 66          | The study nurse will call to enquire as to adverse effects, pain score and any other problems, and advice on the next dosage. If the pain has abated significantly the dose will be left at one tablet at night. If not, the dose will be increased to two tablets at night for three nights.                                                                                                                                                                                                               |
| Day 69                  | The study nurse will call to enquire as to adverse effects, pain score and any other problems, and advice on the next dosage. If the pain has abated significantly the dose will be left at two tablet at night. If not, the dose will be increased to three tablets at night for three nights.                                                                                                                                                                                                             |

|                                                                   |                                                                                                                                                                                                                                                                                                                                                                                                                                                            |
|-------------------------------------------------------------------|------------------------------------------------------------------------------------------------------------------------------------------------------------------------------------------------------------------------------------------------------------------------------------------------------------------------------------------------------------------------------------------------------------------------------------------------------------|
| Week 11 day 72                                                    | The study nurse will call to enquire as to adverse effects, pain score and any other problems, and advice on the next dosage. If the pain has abated significantly the dose will be left at three tablets at night. If not, the dose will be increased to four tablets at night for three nights.                                                                                                                                                          |
| Day 75                                                            | The study nurse will call to enquire as to adverse effects, pain score and any other problems, If not, the dose will be increased to six tablets at night.                                                                                                                                                                                                                                                                                                 |
| Day 78                                                            | The study nurse will call to enquire as to adverse effects, pain score and any other problems, and advice to stay on the same dosage for the next 4 weeks.                                                                                                                                                                                                                                                                                                 |
| Visit 12.0 Week 12 day 82                                         | 
5. Visit to study site Check diary, questionnaire administered, medication check, discussion and information as required with participant, reimbursement, referral as required Collection of demographic data(Appendix I)
 
6. Collection of clinical data(Appendix II)
 
7. Assessment of peripheral neuropathy and other symptoms(Appendix III); if present refer to Palliative care
 
8. Assessment of coexisting pain medication
 |
| Day 91                                                            | The study nurse will call to enquire as to adverse effects, pain score and any other problems, and advice to stay on the same dosage for the next 2 weeks                                                                                                                                                                                                                                                                                                  |
| Day 98                                                            | The study nurse will call to enquire as to adverse effects, pain score and any other problems, and advice to stay on the same dosage for the next 1 weeks                                                                                                                                                                                                                                                                                                  |
| Exit procedure Week 15 is the exit visit and visit to study site. | Check diary, questionnaire administered, medication check, pain intensity score, clinical examination and discussion and information as required with participant, reimbursement, referral as required. Information on study results feedback session                                                                                                                                                                                                      |

[figure not shown]

